## **9.4 Outcome measures for analysis**

The statistical description includes mean, standard deviation, median, quartile and maximum value and minimum value of continuous variables, and frequency and percentile of categorical variables. All data will be examined for outliers and missing values. Some variables will be transformed. Analysis will be based on the data distribution and research issues. Continuous variables will be analyzed with ANOVA for randomized block design, paired t-test and rank sum test to compare the changes from baseline within the same group. ANOVA and rank sum test will be used to examine the differences between groups for continuous variables. Categorical variables will be analyzed with Pearson chi-square test, CMH chi-square test or Fisher probabilities to compare the differences between groups. A P value of  $<0.05$  is considered to be statistically significant except for extra specification.

**Demographic and baseline characteristics:** Frequency distribution and summarized statistical data of demographic and baseline variables will be analyzed individually according to different treatment groups in efficacy analysis.

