| 
 
1. To evaluate the efficacy of adjunctive saxagliptin (and vitamin D3) to metformin (and insulin) on <math>\beta</math>-cell function in compared with metformin (and insulin) in LADA patients.
 
2. To evaluate the efficacy of adjunctive saxagliptin (and vitamin D3) to metformin (and insulin) on glycemic control /insulin-sparing/changes of autoantibody titer in compared with metformin (and insulin) in LADA patients.
 
 | 
 
1. Absolute changes from baseline in fasting C-peptide levels at week 26, 52 and 78.
 
2. Absolute changes from baseline in C-peptide at 60-min and 120-min (AUC) during a mixed-meal tolerance test at week 26, 52, 78 and 104.
 
3. The proportion of subjects with increased (decreased, unchanged) fasting or post-stimulus C-peptide level compared with baseline after 104 weeks of treatment.
 
4. The proportion of subjects with increased C-peptide pre-and post mixed-meal tolerance test (Delta C-peptide) after 104 weeks of treatment.
 
5. Changes of HbA1c levels from baseline
 
 |

|                                                                                                                                                                                                                                                                                                                                                                                                                                                                                  |                                                                                                                                                                                                                                                                                                                                                                                                                                     |

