|----------------------------------------------------------------------------------------------------------------------------------------------------------------------------------------------------------------------------------------------------------------------------------------------------------------------------------------------------------------------------------------------------------------------------------------------------------------------------------|-------------------------------------------------------------------------------------------------------------------------------------------------------------------------------------------------------------------------------------------------------------------------------------------------------------------------------------------------------------------------------------------------------------------------------------|
|                                                                                                                                                                                                                                                                                                                                                                                                                                                                                  | 
at week 26, 52, 78 and 104.
 
6. The proportion of participants responding to hypoglycemic agents (defined as HbA1c<7%) after 104 weeks of treatment.
 
7. Changes of average daily insulin dose from baseline at week 26, 52, 78 and 104.
 
8. Changes of GADA titers from baseline at week 52 and 104.
 
9. Absolute changes of body weight and BMI Level from baseline at week 26, 52, 78 and 104.
 |

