## **Statistical methods**

All data are entered into SAS 9.3 software (SAS Institute Inc., Cary, NC, USA). The measurements will be calculated mean, standard deviation, median, quartile, minimum, and maximum. Categorical variables will describe as frequency and percentage. Changes from baseline in primary and secondary endpoints will be analyzed using a covariance pattern model, with treatment as classification variables and baseline value as a covariate. Point estimates and 95% confidence intervals (CIs) for the mean change within each treatment group, as well as for the differences in mean change between the two groups will be estimated. Differences in categorical variables will be analyzed using Pearson  $\chi^2$ , CMH  $\chi^2$  or Fisher probabilities. For primary outcomes,  $p < 0.025$  will be considered as significant. Other outcomes  $p < 0.05$  will be considered as significantly.

Adverse events (AEs) will be summarized. The incidence of adverse events will be summarized by body system organ class and preferred term. Analyses for safety and tolerability endpoints will be summarized using descriptive statistics for continuous variables or frequency counts and percentages for categorical variables. All conclusions will be based on final analysis rather than the interim analysis.

---

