## **4.3 Method of Randomization**

A central randomization system will be adopted, and the study population will be stratified based on the following: fasting C-peptide (FCP)  $\geq 300$  pmol/L and  $< 300$  pmol/L; GADA titer  $\geq 0.3$  and  $< 0.3$  index; BMI  $\geq 25$  kg/m^2 and  $< 25$  kg/m^2. Patients will be randomized 1:1:1 into the following three intervention groups: metformin (and insulin), metformin (and insulin) plus saxagliptin, metformin (and insulin) plus saxagliptin and vitamin D3.

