### **7.1 Efficacy assessments**

- C-peptide: they were tested in a central laboratory. Detection was carried out by chemiluminescence using a commercially available kit (Adiva Centaur System, Siemens, Germany). The intra- and inter-assay variation coefficients were 3.7-4.1% and 1.0-3.3% respectively. Fasting serum C-peptide, peak C-peptide (60 minutes) and the area under curve of the 120-minute C-peptide were measured using a mixed meal tolerance test (MMTT, as follows). Detection is performed at V1, V8, V14, V20, and V26.
- HbA1c: it was tested in local medical center laboratories independently. The measurements are performed at V1, V5, V8, V14, V20, and V26.
- MMTT: participants will be provided with instant noodles with the net weight of 75g, and without any condiment oil. Timing of the 1-hour and 2-hour postprandial tests starts from the beginning of the meal. Participants will be required to finish the meal in 15 minutes once started. Three days before the MMTT, the participants must be reminded to assure at least 150 grams of carbohydrate intake every day. Before visiting, the participants must have fasted for at least 8 hours and abstained from tobacco, alcohol and caffeine for at least 24 hours. Confirm that the patient did not take saxagliptin 3 days before visit, and did not take the insulin injection in the morning of the visit date.

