#### **9.4.2 Analysis of the secondary variable(s)**

The secondary endpoints including other parameters of  $\beta$ -cell function, for example C-peptide changes during MMTT. Glycaemic control parameters including HbA1c, FPG and PPG. Insulin-sparing effect is the difference of daily insulin dosage. One-way ANOVA will be used to examine the baseline data and the changes in AUC during MMTT, FPG, PPG, HbA1c and insulin dose between groups. The changes of secondary variables described above from the baseline within the same group and between groups will be analyzed with repeated measurement analysis of variance. The frequency counts

and percentages will be summarized on proportion of patients achieving  $\beta$ -cell function protection and glycaemic control.

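### Proportion endpoints: two of the three listed tests ignore baseline and CMH has no strata, so power may be lost if baseline is prognostic

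*Protocol*

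**What the plan says.** Section 9.4 gives one general sentence for all categorical outcomes: "Categorical variables will be analyzed with Pearson chi-square test, CMH chi-square test or Fisher probabilities to compare the differences between groups". The synopsis, under Statistical methods, lists the same three tests. Neither place says which test goes with which endpoint or names strata for CMH.

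The proportion endpoints affected include "The proportion of participants responding to hypoglycemic agents", defined as HbA1c below 7% at week 104, and "The proportion of subjects with increased (decreased, unchanged) fasting or post-stimulus C-peptide level compared with baseline after 104 weeks of treatment". Both are secondary. Both recur as exploratory outcomes for the vitamin D3 add-on comparison.

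Section 9.4.2, which deals with the secondary variables, names no test for them. It says that frequency counts "and percentages will be summarized on proportion of patients achieving" beta-cell protection and glycaemic control, and 9.4.4 says the same for the exploratory comparison.

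For changes from baseline, the synopsis plans a model "with treatment as classification variables and baseline value as a covariate". Baseline data exist for the proportions too. For HbA1c, section 7.1 states: "The measurements are performed at V1, V5, V8, V14, V20, and V26". C-peptide is also measured at V1. Randomisation (4.3) is stratified on fasting C-peptide (300 pmol/L), GADA titre (0.3 index) and BMI (25 kg/m²). HbA1c is not a stratification factor.

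**The concern.** A test of two proportions that ignores a prognostic baseline value is valid but less sensitive than an adjusted test on the same subjects. The baseline of each dichotomised variable is collected, and so are the three randomisation factors. Yet no baseline-adjusted model is named for any proportion, and the one listed test that can adjust has nothing specified to adjust for. The synopsis uses the baseline value when a variable is analysed as a change, but not when the same variable is cut into categories.

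At stake is the sensitivity of the secondary and exploratory responder comparisons. In an open-label trial it would also be better not to leave an open choice among three tests.

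**Working it through.** **The plan's own figure.** No power or sample size is stated for any proportion endpoint. The only figure is for the primary endpoint, and it reproduces:
- SD = √((84.5² + 52.8²)/2) = 70.46; difference = 149.2 − 108.4 = 40.8; two-sided α = 0.025; power 90%.
- n = 2[(2.241 + 1.282) × 70.46/40.8]² + 2.241²/4 = 75.28, rounded up to 76; 76/0.8 = 95; 100 set.
- With 20% drop-out, 100 per arm leaves 80. That is the arm size used below, at two-sided 0.05.

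**Assumptions.** The protocol gives no responder rates, no HbA1c SD and no baseline/week-104 correlation. All of these are assumed.

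**Check A: HbA1c below 7% from a continuous model.** Week-104 mean 7.2, SD 1.2, arm effect 0.5.
- Closed form, taking 7.2 as the comparator mean: P(<7) = Φ(−0.2/1.2) = 0.434 against Φ(0.3/1.2) = 0.599, a difference of 0.165.
- Pooled standard error √(2 × 0.516 × 0.484/80) = 0.0790; unpooled 0.0779.
- Unadjusted power ≈ Φ((0.165 − 1.96 × 0.0790)/0.0779) ≈ 55%.
- Two simulations (1,500 and 3,000 runs) gave 53–55% for Pearson. Fisher gave 47–50%, with null rejection of only 3.1–3.7%.

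| Baseline/week-104 correlation | Logistic with baseline | Gain over 54% |
|---|---|---|
| 0.3 | 58–59% | 4–5 points |
| 0.5 | 63–65% | 9–11 |
| 0.6 | 65–68% | 11–14 |
| 0.7 | 71–72% | 17–18 |

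**Check B: a logistic model.** Response 40% against 60%, 4,000 runs. The CMH test uses two strata split at the median of the outcome's own baseline. Closed-form unadjusted power is 72%.

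| Log-odds per SD of baseline (AUC) | Pearson | CMH | Logistic | Logistic − Pearson |
|---|---|---|---|---|
| 0 | 72.5% | 72.6% | 73.0% | 0.5 points |
| 0.5 (0.64) | 71.6% | 73.2% | 74.9% | 3.3 |
| 1.0 (0.74) | 70.6% | 76.9% | 79.3% | 8.7 |
| 1.5 (0.82) | 71.1% | 80.8% | 84.9% | 13.8 |
| 2.0 (0.86) | 70.9% | 86.4% | 90.3% | 19.4 |

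- At 50% against 70% the gains over Pearson are 1.5, 2.6, 8.6, 13.9 and 18.0 points.
- Against the closed-form 72%, the moderate case gains 79.3 − 72.0 = 7.3 points.
- At moderate or greater strength, this CMH recovers part of the gain. For example, (76.9 − 70.6)/(79.3 − 70.6) = 72%, and for 50% against 70%, (76.8 − 71.9)/(80.5 − 71.9) = 57%. The overall range is roughly half to four fifths.
- Null rejection was 0.04–0.06 for Pearson, CMH and logistic.

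Together, the two checks give about 0–5 points for a weak baseline, 7–11 for moderate and 14–19 for strong.

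**Check C: C-peptide increased or not.** Here baseline is part of the outcome. One simulation assumed a 0.4 SD effect, a 0.3 SD decline and 80 per arm. Pearson against adjusted power was 40% v 50%, 51% v 59%, 73% v 79% and 87% v 90% at correlations 0.3, 0.5, 0.7 and 0.8. A gain remains, but it falls from 10 points to 3 as correlation rises, the opposite pattern to HbA1c. The HbA1c figures therefore do not carry over.

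**The case against.** The strongest reply is that CMH is the standard stratified test and is already listed, so the protocol does not exclude adjustment. Strata and the matching of tests to endpoints can be left to the SAP, which section 9.1 promises before database lock and which is not shown. This stands in part. A reader might infer that the plan is confined to unadjusted tests, and the text does not support that. What remains is that the protocol itself states the tests, two of the three cannot adjust, and no baseline-adjusted model is among them.

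A reader might also infer that baseline largely decides these outcomes. Nothing in the protocol shows that. Basic medication is started or adjusted from Visit 1, and insulin may be adjusted towards a glucose target for 104 weeks, which could weaken the link between baseline and final HbA1c. The low end of the range is therefore possible.

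The contrast with the continuous analyses must also be kept narrow. Baseline as a covariate for secondary changes appears only in the synopsis. Sections 9.4 and 9.4.2 name ANOVA, rank sum and repeated-measures methods without it. Finally, 9.4.2 promises only a summary of the proportions. That is correct, but 9.4 and the synopsis give tests and a significance level for the same kind of variable, so the wording needs settling either way.

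**Conclusion.** The point holds as a minor matter of efficiency. The listed tests are valid, the endpoints are secondary or exploratory, and neither the primary analysis nor the sample size is touched. What is lost is power, and only if baseline is prognostic. With 80 per arm, the HbA1c responder comparison gains between nothing and 19 points. Where it falls in that range depends on a correlation that the protocol does not give, and also on the assumed response rates and effects. For the C-peptide categories a gain is plausible, but its size rests on one further set of assumptions and follows a different pattern.

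**What to change.** In the synopsis (Statistical methods) and sections 9.4 and 9.4.2, name one test for each proportion endpoint. Use logistic regression, ordinal for increased/unchanged/decreased, with treatment, the continuous baseline of that variable and the three randomisation factors. Report the standardised risk difference with its confidence interval, since the odds ratio from such a model is conditional on the covariates. Align the matching sentence in 9.4.4.

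For sparse cells, name CMH as the fallback with its strata stated. They must include a split on the baseline of the variable concerned, which is baseline HbA1c for the HbA1c endpoint. Stratifying on fasting C-peptide, GADA and BMI alone would not adjust for HbA1c.

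The cost is a sentence or so in each place and routine code, with no new data. The drawback is that a model-based test, with a proportional-odds assumption in the ordinal case, replaces a simple table test.

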### **9.4.1 Analysis of the primary variable(s)**

The primary endpoints in the study are absolute fasting C-peptide changes between saxagliptin + metformin (and insulin) group vs. metformin (and insulin) group, and vitamin D + saxagliptin + metformin (and insulin) group vs. metformin (and insulin) group from baseline after 104 weeks of treatment. The primary endpoint will be analyzed utilizing mixed model repeated measures (MMRM) on full analysis set (FAS). Within the framework of MMRM, point estimations and 2-sided 95% CIs will be presented at each visit for the mean change within each treatment group as well as the difference of the mean change between treatment groups. The following hypothesis will be tested to establish superiority:

### **Hypothesis Testing in Superiority Trial:**

Superiority trials are designed to show a treatment effect between saxagliptin (combined with vitamin D3) + metformin (and insulin) group and metformin (and insulin) alone group. Treatment with saxagliptin (combined with vitamin D3) + metformin (and insulin) is supposed to be superior. This superiority trial can be expressed by two hypotheses:

- Null hypothesis  $H_0: \mu_S - \mu_I = 0$ , which states that there is no difference between saxagliptin (and vitamin D3) + metformin (and insulin) group and metformin (and insulin) alone group in terms of outcome variables;
- Alternate hypothesis  $H_a: \mu_S - \mu_I \neq 0$ , which states that there is a difference.

The type I error rate for each hypothesis test is adjusted to be 0.025 considering saxagliptin + metformin (and insulin) group vs. metformin (and insulin) group and saxagliptin + vitamin D3 + metformin (and insulin) group vs. metformin (and insulin) group involved.

To determine whether saxagliptin was effective, the confidence intervals for the two groups should be constructed. If the two-tailed upper limitation of 97.5% CI is less than 0, then null hypothesis  $H_0$  is rejected and a “win” declared if the absolute change of fasting C-peptide is 100 pmol/L or less in Group B in the 104 weeks. A sensitivity analysis will also be performed on the primary endpoint with last observation carried forward (LOCF) for missing values by analysis of covariance (ANCOVA). The effect of “drop-outs” (subject withdrawals), covariates (age, gender, physiologic status), and protocol violations will be analyzed by statistical models.

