### 9.2 Sample size estimation

The sample size calculations were performed based on the primary variable “absolute change in fasting C-peptide from baseline to 104-week”.

Because there is no study for the effect of Saxagliptin combined with vitamin D3 on  $\beta$ -cell function of diabetes patients, the sample size calculations in this study is based on early published literature comparing the effect of sitagliptin combining insulin and insulin therapy alone on  $\beta$ -cell function in LADA patients with the course of diabetes less than 1 year. Our study hypothesis is that saxagliptin will improve the protective effect on  $\beta$ -cell function in LADA treated with metformin (and insulin) than those with metformin (and insulin) alone, and saxagliptin combined with vitamin D will also further improve protective effect on  $\beta$  cell function in LADA treated with metformin (and insulin) than those with metformin (and insulin) alone. The means of effect of insulin treatment group and sitagliptin combining insulin group on fasting C-peptide (extent of fasting C-peptide changing from baseline to 1 year later ) which is the indication of  $\beta$ -cell function are 149.2, 108.4 individually, the standard deviations are 84.5, 52.8 individually. As twice test involved, set two-sided  $\alpha=0.025$  as significance level, and set  $\beta=0.1$  that means the power of test is 90%. According to the formula used to compare the means of two-sample:

$$n = 2 \left[ \frac{(\mu_{\alpha} + \mu_{\beta})}{\delta/\sigma} \right]^2 + \frac{1}{4} \mu_{\alpha}^2$$

Calculating with the formula and above values, we can get the sample size  $n=76$ .

According to calculation with the drop-out rate which is approximate 20%, 95 patients per group are needed. We set 100 cases per group, 300 cases in total.

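### The Bonferroni split for the two primary comparisons is valid but passes on no alpha after a rejection, and the 95% intervals planned for those comparisons do not match the 97.5% decision rule

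*Protocol*

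**What the plan says.** **Alpha.** Protocol 9.4.1, under the superiority hypothesis heading, says: "The type I error rate for each hypothesis test is adjusted to be 0.025", and gives the two comparisons with control as the reason. Section 9.2 uses the same level for the sample size ("As twice test involved, set two-sided" alpha of 0.025, with beta 0.1, for which it adds "that means the power of test is 90" per cent). The synopsis applies p < 0.025 to primary outcomes. None of these places moves alpha from one comparison to the other after a rejection.

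**Decision interval.** The same part of 9.4.1 rejects the null hypothesis when the upper limit of the two-tailed 97.5% CI is below 0. That sentence is introduced as the test of saxagliptin and names only Group B.

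**Presented intervals.** The opening paragraph of 9.4.1 says of the mixed model: "point estimations and 2-sided 95% CIs will be presented at each visit for the mean change within each treatment group". The sentence continues to the differences between groups, so it covers both primary differences at week 104. The synopsis (Statistical methods) has the parallel sentence, "Point estimates and 95% confidence intervals (CIs) for the mean change within each treatment group", also extended to between-group differences. The synopsis mentions no 97.5% interval.

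**The concern.** There are two separate matters.

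First, once one comparison has been rejected at 0.025, the other can be tested at 0.05 without the family-wise error exceeding 5%. The protocol keeps it at 0.025. With two co-listed primary objectives, the chance of establishing both matters, and the fixed split lowers it.

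Second, the protocol sets two interval levels for the same week-104 estimate and does not say which one accompanies the primary result. For any p-value between 0.025 and 0.05, the planned 95% interval excludes 0 while the protocol's own test fails. A report built from the synopsis would show such an interval beside a non-significant primary result.

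**Working it through.** **Inputs**
- Means and SDs, section 9.2: "are 149.2, 108.4 individually, the standard deviations are 84.5, 52.8 individually". Difference 149.2 − 108.4 = 40.8. Root-mean-square SD = √((84.5² + 52.8²)/2) = 70.46.
- Alpha 0.025 two-sided (z = 2.2414) and power 90% (z = 1.2816), section 9.2.
- Allocation, section 4.3: "Patients will be randomized 1:1:1 into the following three intervention groups".
- Assumptions: Group C has the same true difference from control (40.8) as Group B; normal test statistics; no covariate adjustment.

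**Reproducing the plan's sample size.** With the formula in 9.2:

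n = 2 × [(2.2414 + 1.2816) × 70.46/40.8]² + 2.2414²/4 = 74.02 + 1.26 = 75.28, rounded up to 76.

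Dropout: 76/(1 − 0.20) = 95. Both figures agree with the protocol, so the sample size already pays for the split.

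**Correlation of the two comparisons (shared control)**
- Equal SDs of 70.46: 0.5.
- Control SD 84.5 and both active SDs 52.8: 84.5²/(84.5² + 52.8²) = 7140.25/9928.09 = 0.72.

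**Power.** At n = 76, SE = 70.46 × √(2/76) = 11.43, so the expected z is 40.8/11.43 = 3.57. Results from 2,000,000 simulated pairs of z statistics, with both effects at 40.8:

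| Rule | Correlation | Power per comparison | Power for both |
|---|---|---|---|
| Bonferroni | 0.5 | 90.8% | 84.5% |
| Holm | 0.5 | 93.7% | 90.3% |
| Bonferroni | 0.72 | 90.8% | 86.0% |
| Holm | 0.72 | 93.3% | 91.0% |

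At 80 completers per arm (100 less 20%), power for both rises from 86.7–88.0% to 91.9–92.5%.

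If only one effect is real (correlation 0.5, n = 76), power for it is 90.8% under Bonferroni and 91.0% under Holm. The chance of a false claim for the other arm rises from 2.5% to about 4.5%, still inside the 5% family-wise limit.

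**Intervals**
- Unadjusted half-widths at n = 76: 95%, 1.960 × 11.43 = 22.4; 97.5%, 2.2414 × 11.43 = 25.6 (ratio 1.144).
- An observed difference between 22.4 and 25.6 in magnitude gives a 95% interval that excludes 0 and a failed test.
- Under the planned effects this happens for a given comparison with probability 94.6% − 90.8% = 3.8%, and for at least one of the two in 7.1–7.3% of simulated trials.

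**Family-wise error under the null (bivariate normal)**
- Two tests at 0.025, the protocol's rule: 4.2–4.6% over the two correlations.
- Two 95% intervals read as tests: 8.2–9.1%.

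**The case against.** Bonferroni is pre-specified, valid and used consistently in the synopsis, section 9.2 and section 9.4.1. It gives each comparison its 90% power; at 80 completers that power is 92.2%. The protocol sets no power target for winning both. A reader might infer that the split is an error, or that alpha is simply thrown away. The documents do not support this: the choice is between valid procedures, and Bonferroni has one real advantage, namely 97.5% intervals that match its decisions exactly. All of this stands, so the Holm point is an efficiency gain and not a correction. The gain also depends on both effects being real at 40.8, and the simulations leave out the added 100 pmol/L condition that 9.4.1 attaches to a win in Group B.

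A reader might also infer from the 95% intervals that the trial's false-positive rate is 8–9%. That holds only if the 95% intervals are used as tests. The protocol does not use them so: it decides at 97.5%, and the synopsis states p < 0.025.

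It is fair to add that estimation intervals and a decision interval can coexist at different levels, and that table labels are often left to the SAP. But this protocol has already fixed both levels for the same estimate without saying which one accompanies the primary result.

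Finally, Holm with 97.5% intervals creates a mismatch of its own for the comparison tested second. That is true and must be stated in the plan. It can arise only in trials where Holm wins a claim that Bonferroni would have lost.

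**Conclusion.** Both parts hold in a limited form. Holm is never less powerful than the current rule and keeps the family-wise error at or below 5%. Its benefit is about 5 to 6 percentage points for winning both claims and about 2.5 to 3 points per comparison at 76 evaluable per arm. This rests on a true difference of 40.8 in both active arms, which for Group C is assumed and not documented. If only one arm works, the benefit is negligible.

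The interval inconsistency is on the face of the protocol and is a reporting defect. It changes neither the type I error nor the sample size, but in about 7% of trials under the planned effects at least one primary 95% interval would contradict the declared result.

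**What to change.** In 9.4.1 and the synopsis:

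1. Test B vs A and C vs A at week 104 by Holm at overall two-sided 0.05: the smaller p-value against 0.025 and, if significant, the other against 0.05.
2. Restate the rejection rule in 9.4.1 in terms of Holm-adjusted p-values for both comparisons, in place of the fixed 97.5% CI limit.
3. Show 97.5% CIs together with the Holm-adjusted p-values for the two primary week-104 differences, and label all other 95% CIs as unadjusted.
4. State that the second-tested comparison can be significant under Holm while its 97.5% CI includes 0. Under the planned effects at n = 76 this occurs in about 5.0–5.8% of trials, which is the gain in power for both claims (91.0 − 86.0 and 90.3 − 84.5).

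If the sponsor keeps Bonferroni, the minimum change is to name the 97.5% CI for both week-104 primary differences in the opening paragraph of 9.4.1 and in the synopsis.

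The cost is wording only. The sample size stays as it is and becomes slightly conservative under Holm. Because the trial is open-label, the change should be made before database lock and before any comparative C-peptide result is seen.

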## **Sample Size**

The sample size calculations were performed based on the primary variable “absolute change in fasting C-peptide from baseline to week 104”.

---

Because there is no study for the effect of saxagliptin combined with vitamin D3 on  $\beta$ -cell function of diabetes patients, the analysis for power of test in this study is based on the articles about sitagliptin combined with insulin compared to insulin alone on the  $\beta$ -cell function of LADA patients within one year. Since our hypothesis are that saxagliptin will increase the protective effect on  $\beta$ -cell function in LADA treated with metformin (and insulin), and vitamin D3 added on saxagliptin will increase the protective effect on  $\beta$ -cell function in LADA treated with metformin (and insulin), the estimation for sample size is according to the comparison of two sample means. The means of effect of conventional treatment and sitagliptin on fasting C-peptide (the change of fasting C-peptide from baseline at 1 year) which is the indication of  $\beta$ -cell function are 149.2, 108.4, respectively, the standard deviations are 84.5, 52.8 respectively. Set  $\alpha=0.025$  as reaching the statistical difference, and set  $\beta=0.1$ , the power of test is 90%. The minimum sample size is 76. According to calculation with the drop-out rate, which is approximate 20%, 95 patients per group are needed. We set 100 cases per group.

---

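### The win rule asks for a Group B change of 100 pmol/L or less, but the trial is sized on 108.4 in that arm, so on the plan's own figures a win has about an 8% chance, not 90%.

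*Protocol*

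**What the plan says.** The decision rule is in section 9.4.1, under the superiority hypothesis heading. It has two parts. The first is the confidence interval for the difference: "If the two-tailed upper limitation of 97.5% CI is less than 0", the null hypothesis is rejected. The second governs the win, which is "declared if the absolute change of fasting C-peptide is 100 pmol/L or less in Group B in the 104 weeks". On error control the same text says: "The type I error rate for each hypothesis test is adjusted to be 0.025". It names both primary comparisons: saxagliptin against control, and saxagliptin plus vitamin D3 against control.

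The sample size is in section 9.2. It rests on an earlier comparison of insulin alone with sitagliptin plus insulin. The mean changes in fasting C-peptide "are 149.2, 108.4 individually, the standard deviations are 84.5, 52.8 individually", taken as the "extent of fasting C-peptide changing from baseline to 1 year later". The synopsis repeats them: they "are 149.2, 108.4, respectively, the standard deviations are 84.5, 52.8 respectively". With two-sided alpha 0.025 and 90% power, section 9.2 arrives at 76 per group, 95 after 20% dropout, and sets 100.

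The synopsis section on statistical methods judges the primary outcomes on p<0.025 alone and mentions no threshold.

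**The concern.** The threshold of 100 is stricter than the value the plan assumes for the treated arm. If saxagliptin performs exactly as section 9.2 assumes, the Group B mean is expected to miss it. The protocol does not derive the 100, carry it into the power calculation or reconcile it with 108.4.

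This is the success criterion for the primary endpoint. A clearly significant result with a Group B decline near 108 would count as positive under the synopsis and fail to be a win under section 9.4.1. Which of the two governs would then be argued after the data are known. The clause also names only Group B: the second primary comparison has a hypothesis and an alpha, but no corresponding win criterion.

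**Working it through.** **Inputs**
- Control arm: mean change 149.2, SD 84.5 (section 9.2).
- DPP-4 inhibitor arm: mean change 108.4, SD 52.8 (section 9.2).
- Two-sided alpha 0.025 per comparison, power 90% (sections 9.2 and 9.4.1).
- Threshold for a win: 100 pmol/L in Group B (section 9.4.1).
- Group B is the saxagliptin arm. The notes to Table 1 show that Group A gets no investigational drug, saxagliptin alone is listed second in sections 3 and 4.3, and the rule is introduced as the way to judge saxagliptin.

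**Step 1: the plan's own sample size**
- Difference: 149.2 − 108.4 = 40.8.
- Common SD: √[(84.5² + 52.8²)/2] = 70.46.
- Section 9.2 formula: n = 2 × [(2.241 + 1.282)/(40.8/70.46)]² + 2.241²/4 = 74.02 + 1.26 = 75.28, rounded up to 76.
- Dropout: 76/0.80 = 95.

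The stated figures reproduce, so these are the planning values in use.

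**Step 2: chance that Group B meets the threshold**
- Standard error of the Group B mean at n = 76: 52.8/√76 = 6.06.
- P(mean ≤ 100) = Φ((100 − 108.4)/6.06) = Φ(−1.387) = 8.3%.

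**Step 3: chance of meeting the whole rule**

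This is a simulation of 2 million draws with independent normal arm means at the planning values. A win needs the upper 97.5% limit of B minus A below 0 and a Group B mean of 100 or less.

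| Evaluable per group | CI condition alone | Group B mean ≤ 100 | Both |
|---|---|---|---|
| 76 | 90.8% | 8.3% | 8.2% |
| 80 (100 less 20%) | 92.2%–92.3% | 7.7% | 7.7% |
| 95 | 96.0% | 6.0% | 6.0% |
| 100 | 96.8% | 5.6% | 5.6% |

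The joint probability almost equals that of the threshold, because a Group B mean of 100 or less nearly always brings the confidence interval with it. The chance of a win falls as the trial grows, since the threshold lies on the wrong side of the assumed mean. More patients cannot repair this.

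**Step 4: sensitivity**
- Common SD of 70.46 in place of 52.8: threshold met with probability 14.9% at n = 76 and 11.7% at n = 100.
- Baseline adjustment with an assumed correlation of 0.5: 5.5% at n = 76.
- Decline continuing linearly to 2 × 108.4 = 216.8 at 104 weeks (an assumption the protocol does not make): essentially 0.
- True Group B mean needed for a 90% chance of meeting the clause at n = 76: 100 − 1.282 × 6.06 = 92.2 or lower.

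**The case against.** **The win label can be separated from the test.** Section 9.4.1 ties rejection of the null hypothesis to the confidence interval alone, and section 9.2 claims 90% power only for the test. That claim is correct and stands. But the label is then still a stated success criterion with no power behind it, and it disagrees with the synopsis.

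**Change is not defined.** If it is coded with its sign, so that a fall is negative, any fall satisfies the clause and it does nothing. That reading does not rescue the rule: an upper limit below zero for treated minus control would then show a larger fall on saxagliptin, which is harm. Section 1.2 expects smaller changes on treatment, and the planning means are positive and smaller on treatment. Both point to the size of the decline. What stands is that the 8% is conditional on this reading, and that the protocol does not say whether the 100 applies to the observed mean or the model estimate.

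**The planning figures carry no unit.** This is true. They are taken as pmol/L, the only unit the protocol uses for C-peptide.

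**The 108.4 is borrowed.** It is a one-year sitagliptin figure, and the sample-size formula uses only the difference and the SD. With SD 52.8 and n = 76, the clause would be met about 50% of the time at a true mean of 100, 63% at 98 and 90% at 92.2. The result is therefore sensitive to the mean. Still, 108.4 is the protocol's only planning mean for an active arm, and continued decline in year 2 would make the threshold harder to meet.

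**Group C does have a test and an alpha.** This is correct. Only the matching win criterion is missing.

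**A significance-plus-threshold rule can be legitimate.** It can, if the threshold is justified and the trial is powered for the joint rule. Neither has been done here.

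**Conclusion.** The concern holds. On the protocol's own planning values, the rule in section 9.4.1 would be met with probability 8.2% at 76 evaluable per group, 7.7% at 80 and 5.6% at 100. The stated 90% power applies to the difference test only. If the treatment effect is exactly as assumed, the trial would fail to declare a win about 92% of the time. The figure assumes that change means the size of the decline, that the planning values are in pmol/L, that Group B is the saxagliptin arm, and that the borrowed one-year mean and SD apply at 104 weeks. Replacing the SD or allowing for baseline adjustment moves the chance of meeting the threshold only between about 3% and 15%. Under the signed reading the clause is empty and the confidence-interval rule points the wrong way, so the text needs correcting on either reading. Because this is the primary success criterion, it must be fixed before analysis.

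**What to change.** Delete the 100 pmol/L clause from section 9.4.1. State that success is declared separately for B against A and for C against A, each solely when its test at two-sided 0.025 rejects the null hypothesis in favour of the active arm. Say in the same place how change is coded, so that the direction of benefit is unambiguous. If 100 pmol/L is wanted as a benchmark, report the Group B and Group C means against it descriptively, outside the decision rule.

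If the sponsor wishes to keep the threshold as a condition, it must be justified, defined for both active arms and carried into the power calculation. With an assumed mean of 108.4, no sample size can give 90% power for it.

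The recommended change costs one sentence in a protocol amendment, mirrored in the SAP. It adds no patients or procedures, and it brings section 9.4.1 into line with the synopsis and section 9.2.
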